### **5.4.5 Sample Size**

Each web-based survey will include at least 100 women with MS/SLE at the childbearing age (18-45 years) considering pregnancy.

### **5.4.6 Recruitment**

The participants recruited via the websites of the DMSG and Lupus Selbsthilfe e.V. In addition, centres and local self-help organisations will be asked to inform potential participants via mailing lists.

### **5.4.7 Participant timeline**

The mean duration of the participation in the web-based survey will take about 45 minutes.

### **5.4.8 Data analysis and statistical methods**

See 5.3.8 (Questionnaire development and translation: data analysis and statistical methods).

## 5.5 **Development of the decision support tool and the decision coaching programme**

In this part, the development and evaluation of the tools will be exclusively on MS. However, the methodological approach would be suitable for SLE and could be carried out in a subsequent project with additional funding

The **decision support tool** (DST) will consist of a web-based evidence-based patient information platform and a decision aid. Whereas the **decision coaching programme (DCP)** will be based on the web-based patient information platform and a decision coaching programme.

The web-based evidence-based patient information, the decision aid and the coaching programme (training for nurses and the coaching intervention) will be developed based on the steps described above (literature reviews, qualitative interviews, web-based surveys) and previous work (online information platform on immunotherapies (DECIMS-Wiki) and coaching programme (Rahn et al., 2018). The programmes will be developed based on the principles of EBPI (Lühnen J., 2017) and the knowledge transfer will reflect educational concepts (Roth, 1971). Experts and expert patients will be involved in the development.

### ***Decision support tool***

A web-based evidence-based information platform, the DECIMS-Wiki (DECIMS, decision coaching in multiple sclerosis, <http://wiki2.kkn-ms.de/>), on multiple sclerosis focusing immunotherapy options was developed by our group (Rahn et al., 2018). The DECIMS-Wiki is hosted by the German Competence Network Multiple Sclerosis (KKNMS). The decision support tool on motherhood choice will be added to the DECIMS-Wiki as an additional chapter. Therefore, the whole DECIMS-Wiki will be copied and renamed for the feasibility phase and the new chapter will be added. Only the participants of this study will gain access.

The following topics will be addressed by the EBPI (considering results from preliminary work including the systematic review to identify the evidence base):

- Risks of exacerbations and progression of MS due to pregnancy, childbirth and lactation (short and long-term)
- Genetic MS risk for children of women and men with MS
- Meaning of MS for the course of pregnancy and childbirth
- Risks of immunotherapies for the unborn (pregnancy) and new-born (lactation)
- Risk of fertility treatment for the course of MS
- Meaning of the social environment and impact on career of motherhood with MS

The online EBPI will be complemented by a decision aid to facilitate individual preference-based decision-making for the decision support tool group. The decision aid will be printable to allow the participants to share the information with others as for example physicians and relatives.

### ***Decision coaching programme***

#### ***Training course***

The curriculum for the training course for decision coaches will follow the train-the-trainer principle, the knowledge transfer will be guided by established educational theories (Roth, 1971) and concepts and will include six SDM steps following a previously developed immunotherapy decision coaching curriculum (Rahn et al., 2018). It will specifically address the evidence, the

use of the decision support tool and the workbook on motherhood choice. Further, role plays with case examples and simulated patients will be performed to practice decision coaching on motherhood choice using supporting materials.

#### Decision coaching

The coaching will be provided by phone or via a web conference. There will be one decision coaching session up to 1.5 hours per women with MS. The decision coaching will be guided by a workbook on motherhood choice following six SDM steps (Rahn et al., 2018) comprising 1) reviewing the problem, (2) key message, (3) information about pros and cons of each option, (4) expectations of the patient, (5) decision, and (6) arrangements (Elwyn et al., 2001b). Further, the online EBPI will be used during the decision coaching.

The specific aim is the development of the decision coaching programme and the decision support tool. The web-based EBPI will be developed for both inventories (DST and DCP). In addition, a particular decision aid will be created for the DST, whereas a specific workbook on motherhood choice will be designed for guiding the DCP.

## **5.6 Qualitative feasibility testing of the decision support tool and the decision coaching programme**

### **5.6.1 Study setting**

The feasibility testing of the DST will be proceeded by phone or web conference. The training course for the decision coaches will take place in the UKE in Hamburg. In case the infection situation of the Covid-19 pandemic does not allow an in-person training course, the training will be conducted online.

### **5.6.2 Participants**

Selected nurses and neurologists with a MS background will be included. Additionally, expert patients and women with MS considering motherhood will participate. Only persons, who have provided signed informed consent will be included.

### **5.6.3 Procedure**

First of all, the decision support tool and the coaching programme will first be presented selected women with MS, physicians and nurses. During this phase, the programme will be continuously developed based on the feedback using qualitative methods (think aloud, teach-back) (Buber, 2009; DeWalt et al., 2011). The feasibility testing (Bowen et al., 2009) is considered as a test of practicability (e.g. concerning content, graphical presentations, clarity, readability) and acceptance (e.g. concerning illustrations, adequacy of examples, understandability) of the content of the coaching programme and the decision support tool. The interviews will be conducted via Cisco Systems' online meeting software WebEx, provided by the UKE, or telephone. The selected women with MS will be interviewed in focus groups. All interviews will be recorded. During that phase, it will be figured out if the coaching should be delivered by phone or web conference. While telephone coaching can be conducted easily, a web conference would have the benefits of allowing participants to see each other and work together through a possible split of the screen.

### **5.6.4 Expected results**

The specific aim of the qualitative feasibility testing is considered as a continuous revise as well as a test of practicability and acceptance of the coaching programme and the decision support tool.

### **5.6.5 Sample Size**

For the feasibility testing of the DCP and the DST, nurses (n=4), physicians (n=4), expert patients (n=2) and women with MS (n=10) will be included.

### **5.6.6 Recruitment**

The participants for the qualitative feasibility testing will be recruited in Hamburg, Bochum, Kiel and Bonn as well as via mailing lists.

### **5.6.7 Participant timeline**

In the qualitative feasibility testing, the participants (expert patients, PwMS, nurses and physicians) will be interviewed. Each interview will take around 45 – 90 minutes.

### **5.6.8 Data analysis and statistical methods**

Analysis of the qualitative data obtained during the feasibility phase will be conducted after the transcription of the interviews according to thematic content analysis (V. Braun & Clarke, 2014). For details of the thematic analysis see Data analysis and statistical methods 5.2.8.

## **5.7 Randomised pilot**

### **5.7.1 Study setting**

Two MS nurses from two different university centres (Hamburg and Bochum) will be trained for the DCP. There will be two groups; one group receives the decision support tool and the other group the decision coaching programme. The participants will be recruited across Germany.

Reminders are sent via a neutral email address, which is not assigned to the project. The compilation of the declaration of consent (including voluntariness) and the handling of all data collected in the context of the study are carried out according to the recommendations of the Hamburg Chamber of Physicians (Hamburg, 2016).

### **5.7.2 Participants**

Women, aged 18 years or older with suspected (Miller, Chard, & Ciccarelli, 2012) or relapsing-remitting MS (Thompson et al., 2018) considering motherhood are eligible. Women cannot participate when they have no Internet access or information uptake is affected by severe cognitive deficit. In addition, two MS nurses will be trained for the DCP. All participants have to give informed consent in advance.

### **5.7.3 Procedure**

After providing informed consent and filling in the baseline questionnaires (see 5.2.3), a study nurse of the MS outpatient clinic of the University Medical Center Hamburg-Eppendorf will

randomise eligible study participants into the two groups (1:3 allocation ratio) using block randomisation. After successful randomisation, the study nurse will provide the access to the information platform and the DST or DCP to the participating women. The participating women will be blinded as to whether they belong to the DST or DCP group.

Decision support tool: women with MS will receive the decision support tool. They will have access to the tool for two weeks and will be asked to fill in questionnaires after that period. All questionnaires will be sent by post with a stamped addressed envelope.

Decision coaching programme: 2 experienced MS nurses will be trained in the developed motherhood choice decision coaching programme. Afterwards, each nurse will provide the coaching programme for women with MS. It is intended that women will have one coaching session within two weeks after they gained access to the information platform. The coaching sessions will be audiotaped by the nurse. The women with MS will be asked to fill in questionnaires again after the decision coaching session. All questionnaires will be sent by post with a stamped addressed envelope.

At the beginning of their participation in the study, women with MS in both groups will be encouraged to make an appointment with their neurologist to discuss motherhood choice after the intervention.

After they have finished the intervention, at least 10 participants from each group will be interviewed by phone using a semi-structured interview guide addressing the feasibility. It will be addressed as well whether the topic was discussed with a neurologist. The nurses will be interviewed after they have provided the last coaching session at the end of the study. The semi-structured interviews will focus on the feasibility of the whole intervention. The randomised pilot will be conducted according to the CONSORT extension, a guidance for pilots and feasibility trials, which may be followed by a future RCT (Thabane et al., 2016).

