### **5.7.7 Participant timeline**

The participant in both groups will be able to use the information platform for two weeks and receive questionnaires afterwards.

Additionally, participants in the coaching group will receive a decision coaching session by a trained MS nurse with a duration of maximal 1.5 hours within 10-14 days after the received access to the information platform. After the decision coaching session, participants will be asked to fill in some questionnaires (see above).

After they have finished the intervention, at least 10 participants from each group will be interviewed by phone using a semi-structured interview guide addressing the feasibility within four weeks. It will be addressed as well if the topic was discussed with a neurologist. The nurses will be interviewed after they have provided the last coaching session at the end of the study. The semi-structured interviews will focus on the feasibility of the whole intervention.

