## **7 Ethics and dissemination**

### **7.1 Consent or assent**

To take part in the study, each potential participant will be fully informed (orally or in written form) of the aims and requirements of the study, before deciding whether to take part in the study. In case of revoked consent, pseudonymised data will be anonymised and used in this form. A deletion of already anonymized or anonymously obtained data is not possible.

Additionally, written consent has to be obtained by a physician or trained scientific staff in the partaking MS/SLE clinics and MS/SLE practices for the face-to-face encounters or telephone interviews (by email, fax, directly). Concerning the web-based surveys, the participants have to give informed consent online in order to use UNIPARK or LimeSurvey. The consent is specified by the Declaration of Helsinki, and by the GCP Guidelines of the EU.

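### The pilot is described as blinded for participants, but only one arm has a live, recorded nurse session and nothing is described that could conceal this

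*Protocol*

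**What the plan says.** The blinding statement is one sentence in Protocol 5.7.3 (Procedure), directly after the randomisation step: "The participating women will be blinded as to whether they belong to the DST or DCP group".

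The rest of the pilot description separates the arms visibly:

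- **What is allocated (5.7.1):** "one group receives the decision support tool and the other group the decision coaching programme".
- **Contact (5.7.7):** "participants in the coaching group will receive a decision coaching session by a trained MS nurse with a duration of maximal 1.5 hours". The DST arm uses the web platform and has no corresponding session.
- **Mode and length (5.5, Decision coaching):** "The coaching will be provided by phone or via a web conference", and "There will be one decision coaching session up to 1.5 hours per women with MS".
- **Recording (5.7.3):** "The coaching sessions will be audiotaped by the nurse".
- **Materials (5.5, Decision coaching):** "a particular decision aid will be created for the DST, whereas a specific workbook on motherhood choice will be designed for guiding the DCP".

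On consent, section 7.1 requires that each potential participant be "fully informed (orally or in written form) of the aims and requirements of the study" before she decides whether to take part.

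On outcomes, section 5.7.4 lists decisional conflict as a key measure, together with the MCKQ-R, the MPWQ, a process evaluation questionnaire and, in both groups, questionnaires on perceived shared decision-making. Section 5.7.8 makes the analysis primarily descriptive and adds exploratory independent-samples t-tests for decisional conflict, knowledge and MPWQ attitudes and worries.

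**The concern.** A woman who has spent up to an hour and a half in a recorded conversation with a nurse cannot be unaware that she was coached. The sentence on blinding therefore gives the pilot a property that its own procedures rule out, at least in the coaching arm.

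The outcome scales are completed by the women themselves after the intervention. Ratings of conflict, worry and involvement in the decision can respond to knowing that one received the more personal programme, apart from any effect of its content. Section 4.2 also states an expectation that adding coaching gives more positive outcomes, and hopes that the pilot will indicate which approach suits decision-making better. Section 5.7.3 commits the pilot to the CONSORT pilot extension and mentions a possible later RCT. If the sentence stands, readers may treat the between-arm differences on self-rated scales as blinded comparisons.

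**Working it through.** **1. The arms side by side (Protocol 5.5, 5.7.1, 5.7.3, 5.7.5, 5.7.7)**

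| | DST arm | DCP arm |
|---|---|---|
| Planned women | 48 | 2 nurses × 8 = 16 |
| Web information platform | yes | yes |
| Arm-specific material | decision aid | workbook guiding the coaching |
| Live nurse session | none | one, up to 1.5 hours, phone or web conference |
| Audio recording of a session | none | yes |
| Sham or attention-control contact | none described | not applicable |

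The sizes are consistent with the stated allocation: 48 / 16 = 3, total 48 + 16 = 64.

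**2. What each arm can know**

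- *DCP women.* The session itself reveals the intervention. This needs no assumption about consent wording, only that the session takes place as intended.
- *DST women.* Not having a session tells a woman something only if she knows that another programme includes one. Section 7.1 promises information on aims and requirements before consent, and a recorded session with a nurse is a requirement for anyone who may be allocated to it. How the two programmes are described to participants cannot be seen in the text available.

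**3. Which outcomes are exposed**

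- Decisional conflict, the MPWQ and perceived shared decision-making are ratings of the woman's own state or experience, so they are sensitive to expectation.
- The MCKQ-R tests knowledge. Knowing one's arm is less likely to change whether an answer is right.
- Of these, 5.7.8 names decisional conflict, knowledge and the MPWQ for the t-test. Perceived shared decision-making is collected in both arms but is not named there.

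**4. Illustration of scale**

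The protocol gives no significance level, SD or effect size, so no stated figure can be reproduced. Assumptions: two-sided alpha 0.05, equal SDs, all 64 women analysed, no true difference, and a reporting shift of δ SD between arms caused only by knowledge of allocation.

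- Standard error in SD units: √(1/16 + 1/48) = √0.0833 = 0.289.
- Degrees of freedom: 16 + 48 − 2 = 62; critical t about 2.00.
- 95% CI half-width: 2.00 × 0.289 ≈ 0.58 SD.
- Noncentrality: δ / 0.289. The probability of a significant result is taken from both tails of the noncentral t distribution.

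| Assumed shift δ (SD) | Noncentrality | Chance of p < 0.05 |
|---|---|---|
| 0 | 0 | 5% |
| 0.2 | 0.69 | 10.5% |
| 0.3 | 1.04 | 17.6% |
| 0.5 | 1.73 | 40% |

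Every shift in this range is smaller than the 0.58 SD half-width, so the pilot's data could not separate such a shift from a real effect or from chance. The shifts are assumed. Nothing in the protocol says how large they would be.

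**The case against.** The strongest reply is that the sentence may mean something narrower: women might not be told what the other programme contains, which programme is under test, or what the investigators expect. Both arms are active and share the same platform, so this is conceivable. But the sentence says that women are blinded to group membership, not to the hypothesis, and the narrower meaning sits awkwardly with section 7.1. If it was intended, it has to be written down.

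Part of the reply stands. A reader might infer that unblinding is certain for all 64 women, because every DCP woman has a session and no DST woman does. The documents do not support that. The counts describe planned sessions, section 5.7.3 only says that one session is intended, and what DST women know depends on consent wording that is not available.

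A reader might also infer that every comparison is compromised, or that the protocol relies on blinding as a defence against bias. Neither follows. The knowledge score is less exposed, and the protocol nowhere says that blinding protects an outcome.

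It is also fair to say that this is a feasibility pilot with a mainly descriptive analysis, and that no sample size, decision rule or confirmatory test rests on blinding. The hypothesis in section 4.2 concerns a decision aid with coaching against a decision aid alone. The pilot compares the information platform plus coaching with the platform plus a decision aid, so that hypothesis supports the expectation argument only loosely.

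**Conclusion.** The point holds. Participant blinding is stated in 5.7.3, and the design described in 5.5, 5.7.3 and 5.7.7 does not have it. For the coaching arm this follows from the protocol alone. For the DST arm it holds to the extent that the consent information describes both programmes, which section 7.1 makes likely but does not settle.

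The consequence is moderate. It affects how the between-arm differences in decisional conflict, MPWQ and perceived shared decision-making can be read. It bears less on the MCKQ-R and leaves the feasibility aims largely untouched. The direction and size of any bias are unknown. The 10.5% to 40% range is conditional on the assumed shifts and the assumed 5% level, and is not an estimate for this trial. The correction should still be made, because blinding is a design statement that the protocol itself makes and that its pilot report could carry forward.

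**What to change.** 1. **5.7.3:** replace the blinding sentence with, for example: *Participants are not blinded to the intervention they receive (open-label).* If something narrower is concealed, such as the study hypothesis, state exactly what is concealed, from whom and until when, and how this agrees with the information promised in 7.1.
2. **5.7.8:** add, for example: *Between-group differences on self-reported scales (decisional conflict, MPWQ, perceived shared decision-making) may partly reflect expectation and will be interpreted as unblinded, exploratory comparisons.*

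Baseline questionnaires already precede randomisation in 5.7.3, so nothing needs to be added there.

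The cost is two sentences of protocol text and a less favourable risk-of-bias statement in the report. Sample size, allocation, procedures and all stated figures stay as they are.

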#### **5.7.4 Expected results**

The following outcomes will be measured in both groups. Decisional conflict (Buchholz 2011) was the primary outcome measure in the study of Prunty et al (M. C. Prunty et al., 2008) on motherhood choice in women with MS and will be applied as a key outcome measure in this project to explore possible effects. Further, knowledge (MCKQ-R) (M. C. Prunty et al., 2008) and attitude and worries towards pregnancy will be assessed (MPWQ). A process evaluation questionnaire addressing the feasibility of the intervention will be developed and women will be asked to fill in after the corresponding intervention. Here, also possible unintended consequences like anxiety towards immunotherapies are addressed. In addition, a slightly modified version of the Control Preference Scale (CPS) (Degner et al., 1997) will be included to assess the women's preferences for involvement in decisions about immunotherapies when they want to have a child.

Further, after the coaching sessions, the exploratory ratings of the extent of SDM (explored with MAPPIN'SDM) (Kasper, Hoffmann, Heesen, Köpke, & Geiger, 2012) will be conducted based on an audio-analysis. MAPPIN'SDM enables to calculate convergent validities between assessments from different perspectives (here e.g. patient, MS nurse and reviewer). Additionally, perceived SDM will be addressed in both groups by questionnaires.

#### **5.7.5 Sample Size**

For the decision support tool pilot, 48 patients will be recruited.

For the decision coaching programme, two groups will be formed, each group with n=1 nurse and n=8 women with MS, so in total n=2 nurses and n=16 women with MS.

### **5.7.6 Recruitment**

Participants will be recruited online via MS groups and self-help organizations.

### **5.7.7 Participant timeline**

The participant in both groups will be able to use the information platform for two weeks and receive questionnaires afterwards.

Additionally, participants in the coaching group will receive a decision coaching session by a trained MS nurse with a duration of maximal 1.5 hours within 10-14 days after the received access to the information platform. After the decision coaching session, participants will be asked to fill in some questionnaires (see above).

After they have finished the intervention, at least 10 participants from each group will be interviewed by phone using a semi-structured interview guide addressing the feasibility within four weeks. It will be addressed as well if the topic was discussed with a neurologist. The nurses will be interviewed after they have provided the last coaching session at the end of the study. The semi-structured interviews will focus on the feasibility of the whole intervention.

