## 6 Data management

All data gained within the study will be assessed anonymously or will be pseudonymised and there will be no possibility to link data to persons without access to the code list.

The recorded interviews will be deleted after transcription and will be archived in anonymised and transcribed form. All electronic data from the web-based surveys will be collected anonymously via the secure online platform UNIPARK or LimeSurvey.

Survey data, collected by the webtool LimeSurvey, will be stored on a server of the LimeSurvey GmbH in Germany. LimeSurvey GmbH claims to be compliant with the General Data Protection Regulation (GDPR; Datenschutzgrundverordnung) (LimeSurvey GmbH, 2021). An agreement on commissioned processing in accordance with Art. 28 GDPR is in preparation. Only authorised persons will have access to the survey data.

Access to the web-based EBPI will be pseudonymised, but the email-address is saved by the system. Through the personal access of patients to the decision support tool based on a personal account (sent via email), it will be possible to individually track the use of the tool (e.g. frequency, use of different parts), which will be used for evaluation. This will be performed with Piwik, an encapsulated plugin to the Joomla platform, where the system is hosted by the KKNMS. Therefore, the user IP addresses will be stored by the system but shielded to anyone but the system administration by [name] and [name]. However, data analyses will be based on pseudonyms.

The personal data as well as the anonymously obtained data in the study and the pseudonymised data will be stored at the archive of the University Medical Center Hamburg-Eppendorf (UKE) for a period of ten years.

Access to the original data and pseudonymised data is only granted to authorised employees of Institute of Neuroimmunology and Multiple Sclerosis. On request, the pseudonymised data can be viewed for traceability and further research.

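### Pilot interviews in both arms, and on one wording the coaching-arm questionnaires, depend on completing the intervention, so women who miss coaching may give no feedback and feasibility may be overstated

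*Protocol*

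**What the plan says.** **Interviews.** Sections 5.7.3 and 5.7.7 give the same rule for both arms. The timeline section puts it this way: "After they have finished the intervention, at least 10 participants from each group will be interviewed by phone". Section 5.7.7 adds that this happens within four weeks. No interview is described for a woman who stops early or never starts.

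**Questionnaires.** The trigger differs by arm and by section.
- DST arm, 5.7.3: "They will have access to the tool for two weeks and will be asked to fill in questionnaires after that period".
- DCP arm, 5.7.3: "The women with MS will be asked to fill in questionnaires again after the decision coaching session".
- Both arms, 5.7.7: "The participant in both groups will be able to use the information platform for two weeks and receive questionnaires afterwards". The same section then also asks coaching participants for questionnaires after their session.
- Process evaluation questionnaire, 5.7.4: "women will be asked to fill in after the corresponding intervention". It also covers possible unintended consequences.

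**Other evidence on use.** Section 6 says of the web platform: "it will be possible to individually track the use of the tool (e.g. frequency, use of different parts), which will be used for evaluation". The nurses are interviewed at the end of the study about the intervention as a whole (5.7.3, 5.7.7).

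**Analysis.** Section 5.7.8 plans mainly descriptive analysis, exploratory two-sample t-tests between the arms on decisional conflict, knowledge and attitude/worries, thematic analysis of the interviews, and a joint display of the two kinds of data.

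**The concern.** The synopsis names feasibility testing as an objective, and 5.7.3 says a full randomised trial may follow. In such a pilot, the women who do not open the platform, do not take up coaching or stop part-way know the most about barriers. An interview rule that starts from completion gives them no defined point of contact.

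The coaching arm is the more exposed. It has an appointment that can be missed, and on the 5.7.3 wording that appointment also triggers the questionnaires. A non-attender could then supply no interview, no process questionnaire and no follow-up outcome. The audio-based ratings of shared decision-making exist only for sessions that took place. A coaching-arm woman who withdrew because the topic distressed her might not be asked about unintended consequences, in a study that expects no adverse effects and plans no audits (7.4).

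The between-arm comparison is also touched. If follow-up is triggered by an event in one arm and by the calendar in the other, the t-tests set women who attended coaching against DST women who returned a form whatever their use of the tool. Those groups may differ for reasons other than the intervention.

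**Working it through.** **1. The plan's own figures (5.7.3, 5.7.5).** DCP: 2 nurses × 8 women = 16. DST: 16 × 3 = 48, as stated. Total 16 + 48 = 64, which agrees with the 1:3 allocation.

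**2. Who reaches each trigger on the stated wording.**

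| Woman | Interview (5.7.3, 5.7.7) | Questionnaires by 5.7.3 | Questionnaires by 5.7.7 |
|---|---|---|---|
| DST, uses tool | yes | yes | yes |
| DST, does not use tool or stops | unclear: depends on what counts as finishing | yes, after two weeks | yes, after two weeks |
| DCP, attends coaching | yes | yes | yes |
| DCP, misses coaching | no route stated | no route stated | yes on the sentence for both arms; no on the after-session sentence |

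The gap is clearest in the last row. For DST questionnaires there is none, and these women are 48/64 = 75% of the pilot.

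**3. What the interview minimum guarantees.** Ten interviews are 10/16 = 62.5% of the DCP arm and 10/48 = 20.8% of the DST arm. The minimum can be met with 6/16 = 37.5% of DCP and 38/48 = 79.2% of DST women never interviewed.

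**4. Would the minimum expose non-completion?** Let d be the share of the DCP arm that does not finish, with women treated as independent. The chance of at least 10 finishers is P = Σ (k = 10 to 16) C(16, k)(1 − d)^k d^(16 − k). The d values are assumptions.

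| d | 10% | 20% | 30% | 37.5% |
|---|---|---|---|---|
| P(at least 10 finishers of 16) | 0.999 | 0.973 | 0.825 | 0.609 |

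Reaching ten therefore says little about how many women were lost.

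**5. Possible size of the distortion (assumptions only).** If only finishers are heard, a favourable proportion is overstated by d × (p_F − p_N), where p_F and p_N are the proportions among finishers and non-finishers. Taking p_F = 90%, the overstatement in percentage points is:

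| p_N | d = 10% | d = 20% | d = 30% | d = 37.5% |
|---|---|---|---|---|
| 90% | 0 | 0 | 0 | 0 |
| 60% | 3 | 6 | 9 | 11 |
| 30% | 6 | 12 | 18 | 23 |
| 0% | 9 | 18 | 27 | 34 |

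The protocol supplies none of these inputs. It also plans no acceptability percentage from the interviews, which are analysed thematically, so the table shows only the scale on which selection can act. In the interviews the practical loss is missing themes, namely the reasons for not starting or stopping.

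**The case against.** Several counter-arguments have force.

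- *The process questionnaire is not restricted to finishers.* A reader might infer from 5.7.4 that both participant-reported sources require completion. The documents do not support that. DST women are asked after a calendar period with no condition on use, and 5.7.7 can be read as extending this to both arms. This objection stands and limits the questionnaire point to the coaching arm.
- *The interview clause may describe timing, not eligibility.* The DST intervention is an access window, which closes for every woman, including one who never logged in. This is a fair reading for DST. It does not help a woman who missed coaching, because the point after which she would be called never arrives, and no alternative is stated.
- *Non-use is observed.* Platform tracking records frequency and parts used, the nurses are interviewed, and practicability and acceptance are tested beforehand (5.6). This stands in part. Tracking as described covers use of the tool, neither coaching attendance nor reasons. Nurses cannot report the reasons of women they never coached, and the earlier testing precedes the randomised pilot.
- *The barriers named in 4.2 are not specific to drop-outs.* Correct: an external nurse and the need for new resources can also be explored with attenders and nurses. Section 4.2 is therefore not used here as support.
- *The choice of interviewees is an operational matter.* Much of it is, but 5.7.3 and 5.7.7 themselves fix when women are approached, and they do not agree on the coaching-arm questionnaires.

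**Conclusion.** The point holds in limited form. Interviews in both arms are tied to finishing. On the 5.7.3 wording, the coaching-arm questionnaires, including the process questionnaire, are tied to the session, while the DST arm has a fixed time. Women who miss coaching may therefore give no feedback, reasons for stopping or not starting are not collected, and the exploratory t-tests may compare differently selected groups.

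A reader might go further and conclude that feasibility *is* overstated. The documents do not show that. It would require non-completion, less favourable views among non-completers, and failure to hear them by any route. No drop-out or acceptability rate is given, so the size is unknown, and it is zero if views do not differ. The part that rests on text alone is the absence of a stated route to coaching non-attenders on the 5.7.3 wording, in an arm of 16 where three such women would already be 3/16 = 19%. The change is worth making because reasons not collected at the time may not be recoverable later.

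**What to change.** 1. Reconcile 5.7.3 with 5.7.7, and the two statements within 5.7.7, so that every randomised woman in both arms receives the questionnaires, including the process questionnaire, at the same fixed time after randomisation or platform access, regardless of tool use or coaching attendance. That time should fall after the period planned for coaching.
2. In 5.7.3 and 5.7.7, add that women who never log in, miss coaching or stop will be invited to a short voluntary telephone interview, in addition to the minimum of ten per group. Platform tracking (section 6) and a record of coaching attendance can identify them.
3. State that the t-tests in 5.7.8 use all randomised women with follow-up questionnaires, by allocated arm.

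The cost is small: a few extra calls within a pilot of 64 and a common mailing date. The downside is that response among these women will probably be lower than among finishers, so the number invited and the number reached should both be reported.
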